## Abstract

**Background:**

Inflammatory neuropathies such as Guillain-Barré syndrome, chronic inflammatory demyelinating polyradiculoneuropathy and paraproteinaemic demyelinating neuropathy are a heterogenous group of peripheral nerve disorders that affect around one to two people per 100,000. Whilst treatments such as intravenous immunoglobulin, plasma exchange and corticosteroids have generally positive results, long-term residual symptoms and associated activity limitations are common.

There is currently no standardised care for patients with ongoing activity limitation and participation restriction as a result of inflammatory neuropathy IN but data from observational studies and a randomised controlled trial suggest that exercise either alone or as part of a multidisciplinary rehabilitation programme may be beneficial in improving activity limitation. Tailoring the intervention for participants following physiotherapy assessment and incorporating patient preference for type and location of exercise may be important.

**Methods/Design:**

The current study is a pragmatic, prospective, parallel observer-blind, randomised controlled trial to evaluate the efficacy and cost-effectiveness of a twelve week tailored home exercise programme versus advice and usual care. Seventy adults with stable immune mediated inflammatory neuropathy IN will be recruited to the study from two main sources: patients attending selected specialist peripheral nerve clinics in the South East and West Midlands of England and people with who access the GAIN charity website or newsletter. Participants will be randomised to receive either advice about exercise and usual care or a 12 week tailored home exercise programme.

The primary outcome of activity limitation and secondary outcomes of fatigue, quality of life, self-efficacy, illness beliefs, mood and physical activity will be assessed via self-report questionnaire at baseline, 12 weeks and 12 months post intervention. Cost effectiveness and cost utility will be assessed via interview at baseline and 12 months post intervention.

Intention to treat analysis will be our primary model for efficacy analysis. Semi-structured interviews will be conducted with a selected sample of participants in order to explore the acceptability of the intervention and factors affecting adherence to the exercise programme.

**Discussion:**

This is the first randomised controlled trial to compare the efficacy and cost-effectiveness of tailored home exercise with advice about exercise and usual care for adults with inflammatory neuropathy.

**Trial registration:**

Current Controlled Trials ISRCTN13311697

## Background

Inflammatory immune mediated neuropathies (IN) are a heterogenous group of peripheral nerve disorders that affect around one to two people per 100,000 [1]. The conditions share an immune-mediated pathophysiological process but the clinical features may vary between conditions. Guillain-Barré syndrome (GBS) is an acute inflammatory polyneuropathy, characterised by rapidly progressive weakness, paralysis and sensory impairment reaching nadir within four weeks of onset [2] such that the majority of patients are unable to walk independently when maximum weakness is reached [3]. Prompt immunomodulatory treatment facilitates earlier recovery that is generally good; with the majority of patients regaining mobility within six to twelve months [4, 5] although residual problems are common and improvements may continue beyond this period [6]. Chronic inflammatory demyelinating polyradiculoneuropathy (CIDP) shares many characteristics with GBS but presents a progressive or relapsing clinical course [7]. There are a number of first-line, combination and supportive treatments available for CIDP, [8] and whilst many patients experience long-term improvement, prognosis is variable and a significant proportion experience ongoing problems [4]. A related condition, paraproteinaemic demyelinating neuropathy (PDN), is characterised by an IgM monoclonal gammopathy with, in about 50 % of cases, serum antibodies to myelin associated glycoprotein. PDN typically presents at an older age than GBS and CIDP, with most cases presenting in the sixth decade or later and symptoms appear similar to CIDP [4]. Despite differences in the initial presentation and time course of GBS, CIDP and PDN, the symptoms experienced by patients and the impact of them on their daily lives are similar.

**Fig. 1 Fig1:**
[figure not shown]
Study design flowchart. Flowchart depicting the process of recruitment, randomisation, data collection and data analysis throughout the trial

At least a third of people with IN experience long term activity limitation. Residual symptoms may still be present many years after recovery from GBS [9–12] and CIDP [13]. One ten year follow-up study [14] showed that 14 % of participants with GBS still had moderate to severe disability and a further 50 % had more minor symptoms, suggesting that residual disability may be life-long. Fatigue is also a very common consequence of IN with between 40 – 80 % of people reporting it [15, 16]. It is often associated with reduced quality of life [15] and greater activity limitation [14].

Persistent disability or fatigue experienced by people with IN adversely affects their working and daily lives, including family and social activities [9, 12, 13, 17–19]. Many people with IN need long-term informal care, often supplemented by support from health and social services [20]. People with IN are high users of services [21] and the personal suffering, as well as health and social care expenditure, increases as people live longer. Therefore, the potential for cost effective self-management programmes aimed at improving disability, mood, societal participation and quality of life should be evaluated.

There is currently no standardised care for patients with ongoing activity limitation and participation restriction as a result of IN. A systematic review of the efficacy of exercise on disability in IN concluded that the current evidence is of poor quality, although progressive resisted strengthening exercise may moderately improve muscle strength [22]. However, observational studies show that supervised aerobic-cycling [23] or unsupervised physiotherapist prescribed community based aerobic and strengthening exercise [24] are associated with an improvement in function, fatigue and quality of life in people with IN. Further, one randomised controlled trial showed that high intensity multi-disciplinary rehabilitation that incorporated physiotherapy for strengthening, endurance and gait training was superior to low-intensity rehabilitation in improving disability in people with GBS several years after recovery [25]. Therefore exercise may be beneficial in improving activity limitation after IN and tailoring the intervention for participants following physiotherapy assessment and incorporating patient preference for type and location of aerobic and strengthening exercise may be important [24].

A tailored approach to exercise prescription based on our pilot study [24] has been developed for the current study in light of social cognition theory [26]. The theory suggests that behaviour is determined by the interaction of current and previous behaviour, social, environmental and cognitive factors such as social support, observational learning or modelling, outcome expectations, self-efficacy, goal setting and self-regulation.

Thus, the current pragmatic randomised controlled trial (RCT) includes a process evaluation that is underpinned by the transtheoretical model (TTM) for behaviour change [27]. The TTM has been shown to be useful in understanding and predicting behaviour change across a range of health behaviours including physical activity [28, 29]. The model proposes a temporal dimension of stages of change (SoC) to describe the sequential change in health related behaviours. The five stages of change are: pre-contemplation, contemplation, preparation, action and maintenance [27, 30]. The model assumes that the likelihood for behavioural change will be dependent on the stage of change at which individuals are currently at and that progress through the stages may be complex. Factors such as self-efficacy and decisional balance (the relative pros and cons of behaviour change) have been consistently shown to increase in a linear fashion alongside this progression through stages [31], suggesting various potential factors to be targeted for intervention.

In order to evaluate the potential role of home exercise for the management of IN, the current RCT will therefore assess the effectiveness, cost effectiveness and cost utility of a tHEP versus advice about exercise and usual care (UC) in a sample of adults with stable IN in the UK.

### Objectives and hypotheses

#### Principal research question

Is a tailored home exercise programme more effective in reducing disability (activity limitation) than advice about exercise and usual care in people with stable inflammatory immune-mediated neuropathy?

Primary hypothesis - a tailored home exercise programme will be more beneficial than advice about exercise and usual care in reducing activity limitation for people with IN.

#### Secondary research questions

What is the cost-effectiveness and cost utility of a tHEP compared with advice about exercise and usual care for people with IN?

Are the health beliefs of people with IN associated with their response to a tHEP versus advice about exercise and usual care?

What are participants’ experiences of a tHEP and which factors influence uptake of and adherence to the programme?

## Methods

### Design

The study is a pragmatic, prospective, parallel observer blind, RCT to evaluate the efficacy and cost-effectiveness of a twelve week tHEP versus advice and usual care. Assessments will be taken at baseline, immediately following the intervention (twelve weeks) and at twelve months. See Fig. 1. The single outcome assessor will remain blinded until the end of the twelve month follow-up period but due to the nature of the intervention, the participants and research physiotherapist will not be blind to allocation.

### Participants

Seventy adults with stable immune mediated IN will be recruited to the study from two main sources: patients attending selected specialist peripheral nerve clinics in the South East and West Midlands of England and people with IN who access the Guillain-Barré syndrome and Associated Inflammatory Neuropathy (GAIN) charity website or newsletter. Potential participants from clinics will be approached by either their doctor or a member of the research team (with the prior consent of the patient’s doctor) and provided with information about the study. Alternatively, they will be sent an invitation letter and information sheet through the post. In both cases, participants will be offered the opportunity to discuss the project and ask questions. Signed consent forms will be returned directly to the research team if they decide to take part, either in person at the clinic, or via the post once the participant has returned home. Potential participants who access GAIN publications will be approached by advertisements on their website and newsletters. Potential participants will contact the research team directly to receive information sheets and to discuss the study prior to consenting to take part.

All potential participants will be screened for compliance with the study inclusion criteria (below) and their diagnosis, IVIg therapy and fitness to participate will be confirmed with their GP or neurologist, with their consent.

### Inclusion/exclusion criteria

Participants will be included if they fulfil the following criteria:They are adults with stable motor neuropathy, with or without sensory neuropathy, as a result of GBS, CIDP or PDN diagnosed using established criteria [32, 33] (and where PDN is defined as the combination of demyelinating neuropathy, serum antibodies to myelin associated glycoprotein, and an IgM monoclonal gammopathy with no evidence of haematological malignancy)They are able to walk 10 m, with or without walking aidsThey are at least one year since onset if they have GBSThey have had no change in self-reported disability, immunotherapy or medication for neuropathic pain in the previous six months (excepting medication dose of azathioprine, which must not have changed for twelve months). Patients receiving regular intravenous immunoglobulin (IVIg) or plasma exchange will be assessed at the same time points after treatment to avoid fluctuations due to time since last treatment. Minor alterations to IVIg therapy in the lead-up to the project will be allowed. A < =10 % change in the average weekly dose will be allowed in the 3 months prior to entry to the trial, and a change of < =20 % in the previous 6 months. If patients have received greater changes, they will still be able to take part but must wait until they meet these criteriaParticipants should not have received physiotherapy treatment in the six months prior to entering the study. Once in the trial, patients may receive additional physiotherapy for other unrelated musculoskeletal problems if necessary but where possible this should be postponed, at least until after the twelve week intervention phaseThey are able to understand spoken and/or written English and are able to communicate responses to questionnaires

Participants will be excluded from the study if they fulfil any of the following criteria:They score zero on the overall neuropathy limitations scale (ONLS) [34], or 1 on the upper limb scale alone (as this would reflect sensory symptoms not affecting function)They have any other unstable medical conditions that a) affect activity limitation b) prevents them from exercising or c) would make it unsafe to exerciseThey are pregnantThey are adults who are unable to consent for themselves

### Sample size

The sample size is based on an 80 % power calculation to detect a difference between mean change in the overall disability sum score (ODSS) [35] of 1 point using a 2 sided test at the 5 % significance level based on a SD of 1.27 from pilot study data [24]. Fifty-four people (27 per group) will be needed; therefore 70 people will be recruited to allow for a 25 % attrition rate at twelve months. The ODSS is a pre-cursor of the ONLS and was used for sample size calculation as this was the recommended outcome measure of disability in IN at the time of the pilot study.

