### Outcome assessment

#### Primary outcome

*Activity limitation* will be assessed using the recently validated Rasch based Overall Disability Scale (RODS) [48]. This 24-item interval scale for activity limitation has greater responsiveness than previous ordinal measures [49]. Scores for the RODS will be collected at baseline, at the end of the twelve week intervention period and at a twelve month follow up.

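### The stated 80 % power is for the ODSS, not for the RODS primary test; it carries over only if the RODS effect is about 0.78 SD or more, and the article gives no RODS figures

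*Protocol article*

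**What the plan says.** In the protocol article, Sample size sets the power at 80 % and words the aim as "to detect a difference between mean change in the overall disability sum score (ODSS) [35] of 1 point using a 2 sided test". The level is 5 %, and the SD of 1.27 is taken from the pilot. The result is given as "Fifty-four people (27 per group) will be needed". Recruitment is then set at 70, on the expectation that a quarter will be lost by twelve months. The section explains that the ODSS preceded the ONLS and was the recommended disability measure when the pilot was run. It does not mention the RODS.

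Under Primary outcome, the article says that this construct "will be assessed using the recently validated Rasch based Overall Disability Scale (RODS"), and describes the RODS as a 24-item interval scale that is more responsive than older ordinal measures. Data analysis (Efficacy of intervention) fits a linear regression of change from baseline to twelve months, with arm and baseline score in the model.

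The ODSS does not appear among the primary, secondary or economic measures. Its successor, the ONLS, is collected as a secondary outcome.

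**The concern.** Power belongs to a particular variable, difference and SD. Here all three are on the ODSS, and the primary test is on a different scale with its own SD. One ODSS point has no stated counterpart in RODS points. The reason given for using the ODSS leads to the ONLS, a secondary outcome, and not to the RODS.

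The article therefore gives a power figure but none for its primary comparison, and no RODS difference is tied to the sample size. What is at stake is how the design is read: what effect on the primary outcome the trial was built to detect. The validity of the test and its type I error are not affected.

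**Working it through.** **Inputs (all from Sample size):** difference δ = 1 ODSS point; SD σ = 1.27, read here as the SD of change; two-sided α = 0.05; power 0.80; 27 per group, 54 in all; 70 recruited; 25 % attrition.

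**1. Reproduce the plan's figure.** The standardised difference is δ/σ = 1/1.27 = 0.787.

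- Normal approximation: n = 2(1.96 + 0.8416)² × 1.27² / 1² = 2 × 7.849 × 1.6129 = 25.3, so 26 per arm.
- Two-sample t-test: 26.3, so 27 per arm and 54 in total. This matches the article.
- Power at 27 per arm: 81.0 % (t-test) or 82.5 % (normal approximation).

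The ODSS calculation is correct.

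**2. What 27 per arm can detect on any scale at 80 % power.**

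- Normal approximation: (1.96 + 0.8416) × √(2/27) = 2.8016 × 0.2722 = 0.76 SD.
- t-test: 0.777, or about 0.78 SD.

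This is the only form in which the result carries to the RODS. In RODS points it is 0.78 × (SD of RODS change), and the article does not give that SD.

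**3. How power depends on the unknown RODS effect.** The effects below are assumptions, apart from 0.787, which is the ODSS value. The test is an unadjusted t-test.

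| Assumed RODS effect (SD of change) | Power at 27 per arm | Per arm for 80 % power |
|---|---|---|
| 0.5 | 44 % | 64 |
| 0.6 | 58 % | 45 |
| 0.7 | 71 % | 34 |
| 0.787 | 81 % | 27 |
| 0.9 | 90 % | 21 |

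The document does not indicate which row applies. The planned model also includes baseline score. If r is the correlation of RODS change with baseline, adjustment reduces the error variance by a factor of about (1 − r²), so these powers lean low. The article gives no r, so the gain cannot be sized.

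**4. Attrition.**

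- 54 / (1 − 0.25) = 72, against 70 stated.
- Loss that still leaves 54 of 70: 1 − 54/70 = 22.9 %.
- Completers at 25 % loss: 70 × 0.75 = 52.5, about 26 per arm. Power on the ODSS assumption is then 79.5 % (t-test).
- The normal-approximation total of 52 would give 52/0.75 = 69.3, or 70. That may be where 70 comes from, but the article starts from 54.

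**The case against.** The strongest reply is that nothing is hidden. The power sentence names the ODSS, the section explains the choice, and the ONLS entry under Secondary outcome measures repeats that the ODSS set the sample size. A careful reader would not take the 80 % as a RODS figure. This stands, and it limits the point to a missing statement for the primary test.

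The second reply is that both scales measure activity limitation and the article calls the RODS the more responsive. On that account, sizing on an older ordinal scale would tend to be conservative, and baseline adjustment could help further. This also stands as to direction. It supplies no number, however, and the sample size section does not use it.

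A reader might infer from the lower rows of the table that the trial is underpowered. The documents do not support that. Those rows are assumed and unadjusted, and the article's one relevant remark points the other way. A reader might also infer that a null RODS result could not be interpreted. It still could, through the effect estimate and its confidence interval; only a pre-stated RODS target is lacking.

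On attrition, the reply is that two participants and half a percentage point of power have no practical consequence. That is accepted, and the item is kept only as a correction of wording.

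**Conclusion.** The concern holds in a limited form. The ODSS arithmetic is sound, but the only stated power is for a scale outside the listed outcomes. For the primary RODS comparison, 80 % holds if the standardised between-group effect is about 0.78 SD of change or more, and the article neither states nor supports that condition with a figure. The threshold assumes 27 completers per arm, an unadjusted two-sample t-test and a two-sided 5 % level.

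Whether actual power on the RODS is above or below 80 % cannot be settled from the document. It would also be wrong to conclude that the calculation powers the ONLS. The article says only that the ONLS was developed from the ODSS and gives no ONLS difference or SD, so that reading makes the same substitution of one scale for another.

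The attrition mismatch is real but minor: 22.9 % tolerated against 25 % stated.

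**What to change.** Leave the sample size and analysis as they are, and revise the Sample size section along these lines:

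- *With 27 completers per arm, an unadjusted two-sided 5 % test of twelve-month change in RODS has 80 % power for a between-group difference of about 0.78 SD of that change. Baseline adjustment may increase this power.*
- Add the equivalent in RODS points (0.78 × SD) if an SD of RODS change is available, with its source.
- Say that the ODSS calculation served as a proxy for the same construct, because ODSS data were what the pilot offered. Do not relabel it as the power for the ONLS.
- Restate the tolerated attrition for 70 recruits as about 23 %. If 25 % is kept as the allowance, the matching figure is 72.

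The cost is wording only. The stated power for the primary test becomes conditional on a standardised effect, which is a weaker claim than an unqualified 80 %.

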### Data analysis

#### Efficacy of intervention

For our primary outcome of activity limitation (RODS) we will adjust for baseline score. For all other outcomes, we will adjust for the severity stratification group using ONLS baseline score, but not for the IVIg stratification group as the likely low numbers will lead to an unstable model.

Intention to treat analysis will be our primary model for efficacy analysis. We will conduct a linear regression of change from baseline to the twelve month follow up and add in both intervention arm and baseline score. A secondary analysis will examine changes between baseline and 12 week follow up. Complete case analysis is most often used but not ideal in this study as we have small numbers. If we have some missing data at twelve month follow up we can attempt to extrapolate based on the data from participants with complete datasets if there is less than 25 % missing data.

Per protocol analysis: If we can identify a suitable cut-off from our measure of adherence we can also run a per protocol analysis by removing those participants from the dataset who did not complete enough of the exercise intervention to be able to show an effect. However, due to low numbers we do not wish to put the analysis at risk by excluding too many.

We will also run an exploratory secondary subgroup analysis of the self-efficacy data in order to see whether self-efficacy influences the efficacy of the intervention. A high/low score threshold will be identified for this purpose.

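### Seventy recruits cover about 23 % attrition, not the stated 25 %, if 54 people are to remain at twelve months; the effect on power is negligible

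*Protocol article*

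**What the plan says.** All the figures are in the Sample size section of the Protocol article. The section opens with "The sample size is based on an 80 % power calculation", and the aim is "to detect a difference between mean change in the overall disability sum score (ODSS") of 1 point, "using a 2 sided test at the 5 % significance level" and "based on a SD of 1.27 from pilot study data". The result is given as "Fifty-four people (27 per group) will be needed", and the next clause reads "therefore 70 people will be recruited to allow for a" 25 % attrition rate at twelve months.

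The target of seventy is repeated in the Abstract and under Participants. The time point for attrition is also that of the main efficacy analysis. Under Efficacy of intervention the protocol states: "We will conduct a linear regression of change from baseline to the twelve month follow up".

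**The concern.** The sentence presents 70 as the consequence of needing 54 people and expecting to lose a quarter of those recruited. The number to recruit is then the number needed divided by the fraction retained, and that gives 72. With 70 recruits and 25 % lost, fewer people remain than the same sentence says are needed.

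Attrition at twelve months falls directly on the main comparison, so the allowance is a figure that the trial relies on and will report. As written, 54 needed, 25 % lost and 70 recruited cannot all hold. What is at stake is the consistency of a headline number. Whether the trial also loses meaningful power is a separate question, checked below.

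**Working it through.** **Inputs (all from the Sample size section).** Difference δ = 1 point in mean ODSS change; SD σ = 1.27; two-sided α = 0.05; power 0.80; 27 per group (54 in total); 70 recruited; 25 % attrition at twelve months.

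**Step 1: reproduce the 54.**

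- Normal approximation: n per group = 2σ²(1.960 + 0.842)²/δ² = 25.3, so 26 per group, 52 in total.
- Two-sample t-test (noncentral t, with df = n₁ + n₂ − 2 and noncentrality δ/[σ√(1/n₁ + 1/n₂)]): the smallest equal group size with at least 80 % power is 27, so 54 in total.

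The t-test reproduces the protocol's figure exactly. The 54 is sound on its stated inputs.

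**Step 2: inflate for attrition.**

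- Recruits needed: 54/(1 − 0.25) = 72, or 36 per group.
- Stated: 70, which is 2 fewer.

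**Step 3: what 70 delivers.**

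- Expected completers at 25 % attrition: 70 × 0.75 = 52.5, that is 52 or 53 people.
- Largest loss that still leaves 54: 70 − 54 = 16, and 16/70 = 22.9 %.
- In whole people, 17 losses (24.3 %) leave 53 and 18 losses (25.7 %) leave 52.

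**Step 4: power at those numbers (ODSS, δ = 1, σ = 1.27, two-sided 5 %, unadjusted t-test).**

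| Completers | Split | Power |
|---|---|---|
| 52 | 26 + 26 | 79.5 % |
| 53 | 26 + 27 | 80.3 % |
| 54 | 27 + 27 | 81.0 % |

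By the normal approximation, 26 + 26 gives 81.0 %.

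The gap is therefore 2 recruits, or 25 − 22.9 = 2.1 percentage points of attrition allowance. Power differs from the stated 80 % by half a point at most, and only if 52 rather than 53 people finish.

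**The case against.** The strongest reply is that the discrepancy is immaterial, and on practical effect that stands. The 25 % is a planning guess, and its uncertainty, like that of a pilot SD, is very likely larger than a 2-point gap in the allowance.

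The planned analysis also adjusts for baseline score, which would if anything raise power above the unadjusted figure. The article gives no correlation between change and baseline, so the following is an assumption. With residual SD 1.27√(1 − r²) and 26 + 26 completers, power is about 79.9 %, 81.1 % and 83.1 % for r = 0.1, 0.2 and 0.3. A modest correlation removes the half-point deficit. The article also contemplates filling in missing twelve-month data when less than 25 % is missing. That provision is too loosely described to count on for restoring 54.

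A second reply is that 70 has a legitimate source: the normal approximation gives 52, and 52/0.75 = 69.3 rounds up to 70. That is possible, but the text states 54 and 27 per group, so it does not make the printed sentence consistent.

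A reader might draw two stronger conclusions, and the document supports neither.

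- **That the trial falls below its stated 80 % power.** This is true only for the t-test with exactly 52 completers, and then by 0.5 points. With 53 completers, or by the normal approximation, 80 % is met.
- **That 54 was wrongly multiplied by 1.25.** That product is 67.5, which rounds up to 68, not 70. The article gives no derivation, so the cause is unknown.

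**Conclusion.** The inconsistency is real and minor. Given 54 people needed at twelve months, 70 recruits cover about 23 % attrition rather than 25 %; covering 25 % would take 72. This follows by division from the printed figures and needs no outside assumption.

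The stated 80 % power is essentially kept at the 52 or 53 completers that 25 % attrition would leave. That conclusion rests on the plan's own δ and SD, roughly equal losses in the two arms and an unadjusted comparison. It concerns the ODSS. The primary outcome is the RODS, so these percentages do not give the power of the primary analysis. Nothing here calls for a change in design, recruitment or analysis.

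**What to change.** Keep 70 and correct the one sentence under Sample size, in either of two ways:

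- state that 70 recruits allow for about 23 % attrition (16 of 70) while leaving 54; or
- keep 25 % and state that about 52 to 53 people are then expected to complete, giving about 80 % power by an unadjusted t-test on the ODSS.

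Either version costs one sentence and no participants, and the seventy in the Abstract and under Participants stays as it is. Raising the target to 72 would also make the figures agree, but the power figures do not require it.
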